**Figure 1 anr370059-fig-0001:**
[figure not shown]
Overview of the external multi‐centre randomised feasibility trial – The CAREFUL study.

### Harms

As major complications occur at high rates in this population, they will be collected and reported as clinical outcomes complications in all cases (see Supporting Information 2). If a local investigator considers that harm may be due to the intervention, an adverse event (AE) or serious adverse event (SAE) will be reported (see Supporting Information 3). This approach is in line with other interventional studies in peri‐operative medicine where high rates of significant complications are expected within the population of interest [17].

### Sample size

Sample sizes of up to 70 participants have been recommended for pilot trials to estimate the standard deviation of a continuous outcome for use in the power calculation of a full‐scale trial [18]. We will randomise 100 participants to allow for an attrition rate of 30% to achieve a minimum of 70 analysable participants at follow‐up.

### Participant selection and enrolment

All patients presenting for orthopaedic trauma surgery with proximal hip fractures at participating sites will be screened, and a log will be maintained on REDCap. Eligibility will be confirmed by a delegated member of the research team and recorded on REDCap.

The CAREFUL Study will employ a three‐layer consent process (patient consent, personal consultee approach and clinical consultee) designed to maximise inclusivity enabling as many patients as possible to participate, including those who lack capacity to consent and potentially benefit from the study (Supporting Information 4, S4).

Participation ends once the participant has completed the 120‐day follow‐up and all other data have been finalised. Participants are free to withdraw from the study following screening and consent, up until the final data collection point.

### Randomisation

Participants will be stratified by site, formed of randomly permuted blocks of randomly varying size using a 1:1 allocation ratio. The allocation sequence will be generated by a statistician at York Trials Unit and not revealed to the study team. The sequences for each site will be uploaded to the REDCap platform. Randomisation will be performed following consent and clinical teams will be informed as early as possible to allow planning of care. Randomisation will only be possible once the consent process is marked as complete on REDCap.

As this feasibility study is testing a pragmatic clinical trial design, clinical teams and patients will know the intervention allocation. Outcome assessors will be blinded to allocation.

### Data collection

All data will be collected electronically and captured in REDCap as per the timeline and Case Record Fields (see Fig. 1, Supporting Information 2). Details of data entry, storage and information governance are provided in Supporting Information 5.

### Statistical analysis plan

Full analyses will be detailed in a statistical analysis plan (SAP), which will be finalised before the end of data collection and reviewed and approved by the trial steering committee. A CONSORT diagram will report the flow of participants through the study. The recruitment rate and 95% confidence interval will be estimated. Outcomes and their completeness will be summarised descriptively by randomised group: continuous data using the mean, standard deviation, median and 25th and 75th percentiles; categorical data using the number of events and percentages. Standard deviations of continuous outcome measures at follow‐up time points will be estimated alongside 80% confidence intervals [18]. Statistical hypothesis testing of effectiveness will not be carried out. Treatment crossovers will be reported with reasons. Instances of unblinding of outcome assessors will be reported descriptively by randomised group.

### Nested qualitative study

To complement the focus groups in work package 2, we will collect additional qualitative information throughout the feasibility study setup and the duration of the study itself.

Data collection will take several forms, including document review of data captured during study setup and conduct and individual interviews:Minutes from trial management group meetings to keep abreast of any challenges that occur during the setup period of the trial, in particular matters arising regarding the recruitment of the four feasibility study sites. The team will then develop strategies to address the identified issues and incorporate this information into the full‐scale trial design.Expression of interest forms regarding site recruitment forms will be reviewed and tailored to capture training needs and any concerns they may have around participating and in the case of those who decline, an option to explain why they have chosen not to participate.Record and attend site initiation visits to note the main concerns sites express.For those sites recruited, verbal feedback will be sought to identify early challenges. The trial team will work with the sites to identify solutions to the issues raised. These solutions will be incorporated into the setup of future sites and full‐scale trial design.Semi‐structured interviews with clinical stakeholders from each pilot trial site (including anaesthetists, surgeons, operating department practitioners and research nurses; up to 16 – approximately four from each site). Data collection will focus on the views and experiences of delivering the intervention and recruiting participants for the trial.Semi‐structured interviews will be conducted with patients or their carers who participate (approximately 10) and decline participation (approximately 5) in the feasibility trial. We will ascertain their views on the study, the intervention, the trial processes and the outcomes which are important to them. Participants will be purposely selected (based on socio‐demographic characteristics, frailty and site) and interviewed following the final outcome measure collection. We are committed to recruiting under‐served populations into the qualitative study. Topic guides will be co‐produced with patient and public members.

Focus group and data from the nested qualitative study will be transcribed. All transcripts and documents collected will be thematically assessed, focusing on the feasibility and design of a full‐scale trial.

In addition, we will use the Implementation Outcomes Framework, focusing on the constructs of acceptability, fidelity, feasibility, adoption, appropriateness and sustainability to enhance our understanding of how to optimise the implementation of the intervention accounting for contextual factors and intended and unintended consequences of doing so, from a staff and patient perspective [19].

### Study monitoring and registration

Study monitoring procedure and sponsorship are reported in Supporting Information 6. The feasibility study has been prospectively registered with the ISRCTN (International Standard Randomised Controlled Trial Number) UK Clinical Study Registry (https://doi.org/10.1186/ISRCTN12558538). The reporting of this protocol is in line with SPIRIT (Standard Protocol Items: Recommendations for Interventional Trials) and the checklist is provided (Supporting information 7).

### Progression criteria

The feasibility study is not powered to detect any difference in clinical or patient‐focused endpoints. Therefore, progression criteria will centre on the deliverability of a definitive trial through evidence obtained in all three work packages. Progression criteria include:Work package 1: The systematic review supports that there is a lack of evidence in this area.Work package 2: Survey and qualitative interviews do not raise significant concerns about acceptability of the intervention to patients and carers, and clinical equipoise or barriers to large‐scale intervention implementation.Work package 3: We will use a red‐amber‐green rating system to classify key elements of feasibility (see Table 1). These will be:○
Site setup: Four sites setup and recruiting patients○
Recruitment: An average of two participants per site recruited per month, ensuring planned recruitment within 15 months.○
Data collection: We anticipate a complete capture of patient‐reported outcome measures (EQ‐5D) at 120 days from 70% or more patients or their proxy.○
Intervention compliance: High rates of intervention compliance and delivery (> 80%).
If all scores are green, this will support progression towards a full trial. Amber scores will indicate that some modifications may be required for a full trial. Any red score will signal concern over feasibility. If none of the scores are green, combined learning from the nested qualitative study and work packages 1 and 2 may indicate how to overcome aspects of feasibility, which may provide reassurance for progression.

**Table 1 anr370059-tbl-0001:** Indicative progression criteria for feasibility. These criteria will be considered alongside findings from the systematic review and the mixed‐methods study to inform progression to a definitive randomised controlled trial.

Domain	Target at end of trial	Green	Amber	Red
Site setup	Four sites setup and recruiting first participant	100% (4 sites)	50–99% (2–3 sites)	< 50% (1 site)
Participant recruitment	Average of 2 participants recruited per site per month	100% (2 per month)	50–99% (1.0–1.9 per month)	< 50% (< 1 per month)
Outcome follow‐up data	Collect ≥ 70% of participant‐reported outcome data at 120 days	≥ 70% (≥ 70 patients)	50–69% (50–69 patients)	< 50% (< 50 patients)
Intervention compliance	≥ 80% of participants receive allocated treatment	≥ 80% (≥ 80 patients)	50–79% (50–79 patients)	< 50% (< 50 patients)

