### Intervention and comparator

Following the randomisation procedure below, participants will be allocated to either:

*(A) Continuous invasive arterial blood pressure monitoring*
Up to three attempts to establish continuous invasive arterial blood pressure monitoring using local anaesthesia before general, neuraxial or regional anaesthesia.Continuous arterial blood pressure monitoring will be maintained until the patient reaches the recovery room, where it may be discontinued or continued at the discretion of the clinical team.

Or

*(B) Standard care*
Three‐ to five‐minute cycles of non‐invasive blood pressure monitoring.

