## Discussion

Intra‐operative hypotension is common [1], associated with harm [2] and appears more severe in older patients living with frailty [4]. Emerging evidence supports that exposure to intra‐operative hypotension may be mitigated by establishing continuous arterial blood pressure monitoring before induction of anaesthesia, be it invasive [20] or continuous non‐invasive [21] for elective major surgery; however, this has not been evaluated in the emergency setting, nor have long‐term clinical or patient‐reported outcome measures been assessed for this intervention.

Recommendations from NAP7, which focused on peri‐operative cardiac arrest, supported a lower threshold for the use of continuous arterial blood pressure monitoring in high‐risk cases, but also acknowledged the lack of an evidence base for this intervention [12]. This was driven by both an observation that multiple objective high‐risk cases progressed to cardiac arrest without the use of continuous blood pressure monitoring [5] and that use of continuous monitoring was low in some high‐risk patient groups [11]. For example, older frail orthopaedic trauma patients had continuous invasive blood pressure monitoring in only 7% of cases at the start of their anaesthetic, and only 12% had continuous monitoring at any point [11, 12]. This is in contrast to other high‐risk groups where rates of use are considerably higher (cardiac surgery 80%, neurosurgery 50%) [12]. Even when adjusted for their estimated SORT score (Surgical Outcomes Risk Tool), those who were objectively high‐risk (5% or greater 30‐day predicted mortality) had only a 16% chance of continuous arterial blood pressure monitoring versus almost all other patient groups where a similar risk profile led to over 50% of cases having arterial monitoring [11]. This stark fact highlights the inequality that older trauma patients living with frailty may be missing the opportunity for patient benefit through what is a cheap and low‐risk intervention.

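### Table 1 scores intervention compliance over both arms together, so the row can be green at roughly 60–72% arterial-line delivery rather than the stated 80%

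*Protocol article*

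**What the plan says.** In Progression criteria, the work package 3 list asks for "High rates of intervention compliance and delivery" above 80% and names no arm. The matching row of Table 1 sets the target as at least 80% "of participants receive allocated treatment". Its bands are also given as counts: green from 80 patients upwards, amber "50–79 patients", red below 50.

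Sample size sets the total at 100, and Randomisation allocates "using a 1:1 allocation ratio". Under Intervention and comparator, arm A is continuous invasive arterial monitoring and arm B is 3–5 minute non-invasive cycles. The Introduction describes such cycles as typical of the UK minimum standard. The Exclusion criteria remove patients for whom arterial monitoring, or 1-minute cuff cycles throughout, is already planned.

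**The concern.** Only arm A is asked to do something new. The Discussion reports that about 7% of comparable patients have an invasive line at the start of anaesthesia, "and only 12% had continuous monitoring at any point". Whether teams can deliver the line is therefore a main practical question for the definitive trial. Arm B asks teams to carry on as usual in patients for whom nothing else was planned. Counting both arms together lets easy compliance in one offset poor delivery in the other. At stake is whether a green rating on this row says what its 80% label suggests about the treatment contrast a definitive trial could achieve.

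**Working it through.** **The plan's own figures.** The target "to achieve a minimum of 70 analysable participants at follow‐up" with 30% attrition gives 70 / (1 − 0.30) = 100, as stated. For the compliance row, 0.80 × 100 = 80 and 0.50 × 100 = 50, which match Table 1. An arm A denominator would give 0.80 × 50 = 40 and 0.50 × 50 = 25, which do not. The row is therefore pooled as written.

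**Inputs.** 50 per arm (100 at 1:1). Control compliance c is not stated and is an assumption. One guide is the Discussion's 7% at the start and 12% at any point: (12 − 7) / 93 = 5.4% gaining continuous monitoring among those without an invasive line at the start, so c of about 95%. The range used is 100% down to a pessimistic 88%.

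**Break-even for green.** Arm A must supply 80 − 50c patients, a proportion of (80 − 50c) / 50 = 1.6 − c. This is below 80% whenever c exceeds 80%.

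**Limit for red.** The total must be 49 or fewer, so arm A can supply at most 49 − 50c.

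**Chance of each colour.** The pooled total is the sum of Bin(50, c) and Bin(50, true arm A delivery), computed by exact convolution. The comparison rule applies the same percentages to arm A alone: green at 40 or more of 50, red below 25.

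| Control compliance c | Arm A count needed for green | As % of 50 | Highest arm A count scoring red | P(green), true delivery 70% | P(green), true delivery 50% | P(red), true delivery 30% |
|---|---|---|---|---|---|---|
| 100% | 30 | 60% | none | 0.95 | 0.10 | 0 |
| 95% | 32.5 | 65% | 1.5 | 0.80 | 0.03 | 0.0001 |
| 90% | 35 | 70% | 4 | 0.56 | 0.009 | 0.003 |
| 88% | 36 | 72% | 5 | 0.46 | 0.005 | 0.008 |
| Arm A rule | 40 | 80% | 24 | 0.08 | 0.000 | 0.998 |

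The counts in columns 2 and 4 use the expected number of compliant controls, hence the fractions at 95%. At c = 100%, the 50 controls alone reach 50 patients, so the row is amber even with no arterial line placed.

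**Threshold wording.** The text requires more than 80%, the table at least 80%. The two differ only at exactly 80 patients.

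**The case against.** A reader might infer that the row cannot detect failed delivery. The figures do not support that: at a true delivery of 50%, the chance of green is at most 0.10, and at 40% it is at most 0.003. Serious failure would nearly always be amber, which the protocol reads as a sign that a full trial may need changes.

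A reader might also treat the colours as a go/no-go rule. Table 1 is headed as indicative, a red score signals concern without stopping the programme, and the ratings are weighed with the other work packages. Information by arm will also exist. Delivery and crossover are listed feasibility objectives, compliance is recorded on the day of surgery, crossovers are reported with their reasons, and staff interviews cover delivery. All of this stands and lowers the severity. None of it changes how the row is scored.

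Control compliance is uncertain too. Clinicians are unblinded and could shorten cuff cycles, and the audit figures neither measure adherence to cycle length nor reflect the trial's exclusions. The size of the effect therefore depends on c. The direction does not, unless control compliance falls to 80% or below.

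Finally, because arm A is described as "Up to three attempts to establish continuous invasive arterial blood pressure monitoring", a reader might infer that three failed attempts would count as compliant. The article does not say so. The row speaks of receiving the allocated treatment, the text adds delivery, and an operational definition can properly sit in the SAP or the supplement on data fields. This is not part of the finding.

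**Conclusion.** The concern holds as a calibration fault. Across assumed control compliance of 88–100%, the pooled row is 8 to 20 percentage points more lenient on arterial-line delivery than its label (80 − 72 and 80 − 60). The red band is impossible at the top of that range and needs about 5 of 50 lines or fewer at the bottom, so delivery well below 50% is rated amber where the stated percentages, read for arm A, would give red. The pooling rests on Table 1's own counts; the sizes rest on 50 per arm, independent binomial compliance and the assumed c. The mismatch between more than 80% and at least 80% is a minor editorial point. Overall this should be fixed, but it does not threaten the feasibility study itself.

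**What to change.** Apply the stated percentages to the arterial-line arm: green at 80% or more of those allocated (at least 40 of 50), amber at 50–79% (25–39), red below 50% (fewer than 25). Report crossover in the standard-care arm as a separate measure. Use at least 80% in both the text and Table 1. Make the change before any results by arm are seen.

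No new data are needed, since compliance and crossovers are already to be recorded. The cost is that green becomes harder to reach. At a true delivery of exactly 80%, the chance of at least 40 of 50 is 0.58, against 0.89 to 1.00 under the pooled row for control compliance of 88–100%. The team should accept that knowingly.

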### Patient and public involvement (PPI) and engagement

A dedicated patient advisory group (PAG) of six to eight committed PPI members with lived experiences will be formed. If needed, PPI members will be signposted to various resources and provided with one‐to‐one training. Most activities will be virtual, enabling participation regardless of geographical location. Patient and public members' time and contributions are fully costed using the National Institute for Health and Care Research (NIHR) guidelines. The patient advisory group and PPI representatives will co‐develop all patient‐facing trial documentation, provide input into the design of qualitative interview guides, advise on matters arising and contribute to the final report.

Patient and public involvement will enable dissemination by supporting the development of leaflets, videos and input to professional societies and groups, as appropriate. The Guidance for Reporting Involvement of Patients and the Public (GRIPP2) reporting checklist will be used to publish the contribution and impact of PPI during the study and will be included in the final study report. An impact log will be maintained to capture and evaluate the overall impact of PPI based on the Public Involvement Impact Assessment Framework.

A stakeholder event at the end of the project as part of our assessment of progression, where PPI and other stakeholders will be fully embedded and central to the outcome. Our public dissemination strategy will be co‐developed with the patient advisory group and they will help with dissemination activities by supporting the development of results leaflets or content for various platforms, including websites, social media, news articles, professional societies and groups and patient charities.

### Dissemination plans

A dissemination and publication policy will be developed with an agreement between the trial management group, including ownership and publication rights. The policy and agreement will ensure that the publication process is organised fairly, balanced and transparently. The trial management group will be responsible for overseeing these arrangements.

We will host a stakeholder event, including PPI representation, to disseminate the findings, gather feedback and guide the development of a definitive study. We will communicate the results to groups including Royal Colleges and the Centre for Peri‐operative Care to inform future iterations of peri‐operative guidelines for patients living with frailty.

Findings will be presented at conferences and meetings, and feedback will be given to the PPI group.

## Discussion

Intra‐operative hypotension is common [1], associated with harm [2] and appears more severe in older patients living with frailty [4]. Emerging evidence supports that exposure to intra‐operative hypotension may be mitigated by establishing continuous arterial blood pressure monitoring before induction of anaesthesia, be it invasive [20] or continuous non‐invasive [21] for elective major surgery; however, this has not been evaluated in the emergency setting, nor have long‐term clinical or patient‐reported outcome measures been assessed for this intervention.

Recommendations from NAP7, which focused on peri‐operative cardiac arrest, supported a lower threshold for the use of continuous arterial blood pressure monitoring in high‐risk cases, but also acknowledged the lack of an evidence base for this intervention [12]. This was driven by both an observation that multiple objective high‐risk cases progressed to cardiac arrest without the use of continuous blood pressure monitoring [5] and that use of continuous monitoring was low in some high‐risk patient groups [11]. For example, older frail orthopaedic trauma patients had continuous invasive blood pressure monitoring in only 7% of cases at the start of their anaesthetic, and only 12% had continuous monitoring at any point [11, 12]. This is in contrast to other high‐risk groups where rates of use are considerably higher (cardiac surgery 80%, neurosurgery 50%) [12]. Even when adjusted for their estimated SORT score (Surgical Outcomes Risk Tool), those who were objectively high‐risk (5% or greater 30‐day predicted mortality) had only a 16% chance of continuous arterial blood pressure monitoring versus almost all other patient groups where a similar risk profile led to over 50% of cases having arterial monitoring [11]. This stark fact highlights the inequality that older trauma patients living with frailty may be missing the opportunity for patient benefit through what is a cheap and low‐risk intervention.

In adult patients undergoing major non‐cardiac surgery, data support that providing continuous blood pressure measurements detects about twice the number of intra‐operative hypotensive episodes versus intermittent non‐invasive monitoring [22]. Further, recent RCT data support that if invasive arterial monitoring is established before the induction of anaesthesia, then the area under a mean arterial pressure of 65 mmHg was reduced from 46 to 15 mmHg effectively reducing the exposure or ‘dose’ of hypotension by 66% [20]. In these studies, no target blood pressure value has been set; inserting an invasive blood pressure monitor was the patient‐protective intervention. Hypotension was managed as per the clinician's choice. Other patient benefits include easy blood gas analysis and sampling, which aid clinical decision‐making. Few studies have investigated if preventing peri‐operative hypotension reduces harm [23, 24]. However, there are suggestions that maintaining blood pressure within 10% of a patient's usual blood pressure reduces the risk of postoperative organ dysfunction as a composite measure [25].

Whilst NAP7 recommended higher rates of continuous monitoring, no study has investigated whether continuous arterial blood pressure monitoring can prevent hypotension and end‐organ injury, or improve the quality of life of older patients living with frailty who require urgent surgery. The CAREFUL study will determine if a definitive trial to address this question is feasible.
